**Fig. 1 Fig1:**
[figure not shown]
DBS for children, targeting the NAcc. **A** DBS extension wires for children are placed with greater length to allow for growth. **B** Coronal representation of DBS lead trajectory, passing through the ALIC and targeting the NAcc. **C** 3D representation of DBS lead trajectory. NAcc (purple), ALIC (yellow), caudate (dark blue), putamen (light blue), and globus pallidus (green)

Patients undergo a postoperative MRI to confirm the position of the electrodes. After the surgery, they are monitored in the hospital for 3–5 days and discharged with the stimulator off. Patients start DBS programming at 4–6 weeks after surgery and visit the joint neurosurgery, neurology DBS clinic at HSC. There is regular monitoring for the development of behavioral, motor, and psychiatric effects from stimulation. During weeks 2–6, there are weekly follow-ups to address any potential complications. The full schedule of events is presented in Table 3.

**Table 3 Tab3:** Follow-up schedule for trial participan ts

		Study period							
		Enrollment	Surgery	Follow-up					Post-trial
Timepoint		Week 8 ± 4 weeks	Baseline W0	Weekly (W1–6) ± 1 day	Every 4 W (W8–56) ± 3 days	Week 12 ± 1 week	Week 26 ± 2 weeks	Week 52 ± 2 weeks	W > 52
Enrollment	Eligibility screen	X							
	Informed consent for trial	X							
	Demographics questionnaire	X							
	Anesthetic evaluation	**X**							
	Informed surgical consent	**X**							
In-hospital treatment and care	Deep brain stimulation leads and IPG insertion		**X**						
	Programming				**X**	**X**	**X**	**X**	**Every 6 months or as indicated**
Imaging	MRI	**X (or earlier)**	**X**						
	CT		**X**						
	FDG-PET (optional)	X						X	
Questionnaires	Children’s Yale-Brown Obsessive-Compulsive Scale in ASD (CYBOCS-ASD)	X		X (week 4)		X	X	X	
	Inventory of Statements about Self-Injury (ISAS)	X		X (week 4)		X	X	X	
	Behavior problems inventory (BPI)	X		X (week 4)		X	X	X	
	Repetitive Behavior Scale-Revised (RBS-R)	X		X (week 4)		X	X	X	
	Quality of Life Scale 9Peds QL	X		X (week 4)		X	X	X	
	Aberrant Behavior Checklist	X		X (week 4)		X	X	X	
Other assessments	Neurosurgery evaluation			X (virtual)	X (virtual)	**X**	**X**	**X**	**Annual follow-up**
	Neuropsychology evaluation	**X**					X	X	As needed
	Actigraphy (optional)	X				X		X	
	Self-injury log	X		X	X	X	X	X	

Bolded cells show standard of care for all pediatric DBS patients

### Sample size and recruitment

In this prospective, controlled trial, six patients are selected to determine safety and initial potential efficacy, as it typical for most DBS early phase trials. There is no control group, and each patient will serve as a comparator for primary outcome measures.

### Feasibility and safety

The trial will be determined feasible if there is > 50% recruitment rate or recruitment of 6 patients in under 36 months as a threshold for progression to a definitive trial. Recruitment rate is measured as the ratio of participants enrolled compared to those who are eligible. New DBS targets typically include 6 patients in pilot trials [45, 46] to establish an initial understanding of effect of therapy through multiple outcomes: clinical, radiographic, and electrophysiologic. There will be additional secondary feasibility outcomes with projected thresholds to determine achievability. These include the proportion of patients who received surgery following enrollment (80%), proportion of patients with full completion of baseline questionnaires (90%), proportion of patients with full completion of multi-modal outcome assessments (i.e., PET, actigraphy) (50%), and percent completion of all clinical outcome data (80%). Families unable to speak English will complete questionnaires through the aid of translators and their completion rate of outcome measures will be compared to English speakers. These data will provide additional information regarding decision-making of progression to a large trial. Any deviance to study protocol or inability to complete clinical questionnaires will be documented with an attempt to understand patient barriers.

The measure of safety outcomes is critical as this routine procedure is being implemented in a new patient population for a novel indication. Immediately peri-operatively in hospital, neurologic complications from surgery (bleeding, seizure) will be monitored and recorded. Longitudinal safety of the intervention will be carefully monitored with weekly phone calls to participants for the first 6 weeks. Participants will be monitored for post-operative complications (i.e., hardware malfunction, signs of infection, unexpected neurologic symptoms) and worsening of severity or frequency of self-injurious behaviors. The expected complication rate is < 10%.

There is no official Data and Safety Monitoring Board (DSMB) for this pilot. Instead, a safety subcommittee consisting of a neurosurgeon, a neurologist, and a developmental pediatrician will meet twice annually to discuss possible safety concerns. This committee would help with the design of the future definitive trial based on the safety concerns raised during this pilot. There are no current stopping criteria outlined, but the safety subcommittee would have the authority to determine cessation of the trial due to unexpected safety concerns.

### Clinical outcome measures

This trial will conduct pre-post analyses to compare frequency and severity of SIB in children and youth with ASD before and after DBS intervention. Clinical outcomes are measured by the change between baseline and 1 year in the following validated scales: Children’s Yale-Brown Obsessive-Compulsive Scale in Autism Spectrum Disorder (CYBOCS-ASD) [47, 48], the Behavior Problems Inventory (BPI) [49], the Inventory of Statements about Self-Injury (ISAS) [50] and the Repetitive Behavior Scale-Revised (RBS-R) [51]. These scales were chosen by expert consensus between developmental pediatricians, neurologists, and the neurosurgical team. Although no scale has specifically been validated for children with ASD and SIB, the combination of these scales studied in children with ASD or all-age patients with repetitive behavior will provide an assessment of responsiveness of DBS over time. Secondary clinical outcomes are measured using the Quality of Life Scale 9Peds QL version 4, Aberrant Behavior Checklist [52, 53], and caregiver logs of repetitive self-injurious behaviors. Time to complete each questionnaire and correlation with quality of life will be useful information in the design of a composite primary objective in larger, future trials.

Patients and caregivers complete scales prior to the intervention and also at week 4, 12, week 26, and week 52. Baseline assessments are completed prior to surgery. Efficacy is determined by the within-subject percent change in the primary outcome scores at 1 year (week 52) following surgery compared to baseline.

Additional outcomes include changes in motor patterns based on actigraphy. Actigraphy is the continuous measurement of an individuals’ movement using a device worn similarly to a watch (Axivity AX3 and Axivity AX6) [54, 55]. The Axivity device can quantify movements and has been validated to detect specific behaviors, such as hand flapping, of patients with ASD with 94.6% accuracy [56]. Children have an actigraph placed on their non-dominant wrist 4 weeks prior to the surgery for a total of 2 weeks of recordings. During specific follow-up visits (weeks 12, 26, and 52), the children have the option to wear the actigraph for 2-week intervals. Markers of stereotypies include maximum and minimum value amplitudes, variance, peak to peak, and entropy fast Fourier transform, to be analyzed using MATLAB (Mathworks, Natick, MA) [54, 56].

Children enrolled in the trial may receive a FDG-PET scan prior to surgery, and 12 months after surgery. PET scanning is optional and for research purposes only, which will be disclosed to all participants. PET scans of pediatric patients with anorexia who received NAcc-DBS has demonstrated the reversal of metabolic abnormalities, such as hypermetabolism in the frontal lobes, hippocampus, and lentiform nucleus [57]. The FDG-PET of participants in the present study may similarly demonstrate changes of metabolism in the brain following NAcc-DBS.

### Follow-up

Evaluation and assessments occur at approximately 22 time points from pre- to 1-year post-surgery (Table 3). Participants are followed weekly after surgery by the medical team between weeks 0–6, and monthly after 8 weeks. There are two required MRI scans that fall under the standard of care, two optional FDG-PET scans, and 3 possible 2-week periods of actigraph recordings. Surveys for the primary clinical outcomes and secondary outcomes are administered once prior to the surgery and four times following surgery. DBS programming starts at approximately 4–6 weeks and reassessment and stimulation changes are planned for weeks 12, 26, and 52 unless there are adverse effects, for which there will be additional programming visits. Ongoing follow-up for safety and DBS programming will occur at HSC until participants turn 18 years old, at which point they will be transitioned to adult care.

### Data management and statistical analysis

Patient information will be kept strictly confidential at all times, and all files related to this study will be password protected and kept on a password protected computer. Patient and caregivers will complete surveys and questionnaires online via a secure email link or on paper. The research team will check the content and completion of the forms monthly. All data will be kept for 25 years following the conclusion of the trial.

This is not a blinded study and all investigators and patients are aware of treatment. There is not blinded stimulation-off or stimulation-on periods after DBS implantation. Recruitment rates will be calculated monthly; the secondary feasibility and safety outcomes would be reported as proportions. Change in SIB and adverse effects will be analyzed longitudinally using comparative statistics. Repeated measures ANOVA and mixed-effects linear regression are used for analysis of clinical measures and changes over the course of 12 months. All efforts are made to reduce missing data with retrospective review and multiple imputation will be employed for unfound data.

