### Goals and objectives

The primary objective of the study is to assess feasibility and safety, measured by recruitment rate, identification of factors impacting follow-up and protocol adherence, and successful implantation. Secondary clinical objectives include change in frequency or severity of SIB following surgery, measured regularly by caregiver-reported questionnaires over the course of 1 year. Additional clinical outcomes include changes quality of life for the patient and their caregiver(s), repetitive motion characteristics as measured with actigraphy, metabolic changes seen through positron emission tomography (PET), and changes on electrophysiologic data. To our knowledge, this is the first prospective trial of DBS for children with SIB and represents the first assessment of a potential surgical treatment for patients with extremely limited therapeutic options.

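### No masking of time point is described for actigraphy processing, although every investigator is declared unblinded and a recorded file could be masked cheaply

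*Protocol article*

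**What the plan says.** The statement on blinding stands under Data management and statistical analysis: "This is not a blinded study and all investigators and patients are aware of treatment". The next sentence adds: "There is not blinded stimulation-off or stimulation-on periods after DBS implantation". Neither sentence distinguishes between outcomes, or between treating staff and whoever processes recorded data.

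Under Goals and objectives, change in self-injurious behaviour (SIB) is "measured regularly by caregiver-reported questionnaires over the course of 1 year". Clinical outcome measures adds that patients and caregivers complete the scales and that caregivers keep logs.

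Actigraphy is introduced in the same section as a further outcome: "Additional outcomes include changes in motor patterns based on actigraphy". A device is worn on the non-dominant wrist for two weeks before surgery, and at specified follow-up visits "the children have the option to wear the actigraph for 2-week intervals". The processing is described in one sentence: "Markers of stereotypies include maximum and minimum value amplitudes, variance, peak to peak, and entropy fast Fourier transform, to be analyzed using MATLAB". No marker is named as leading. The article does not say who does the processing or whether files carry visit labels.

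FDG-PET is also free of caregiver rating, but "PET scanning is optional and for research purposes only", and it measures metabolism rather than behaviour.

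**The concern.** With open stimulation and no control group, expectation can affect every rating that a patient or caregiver completes, and nothing in this design can remove that. An actigraphy file is different. Once recorded, it can be processed by someone who does not know whether it comes from before or after DBS. The blinding statement makes no use of this.

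At stake is the value of the one behavioural measure that does not pass through a caregiver's judgement. The Discussion hopes that several measurement tools will help to shape a composite outcome and that an estimated effect size will help to plan a later trial. Whether a device agrees with the ratings is useful pilot information for that purpose. It is worth less if the choices made in cleaning and summarising the recordings could have been steered by knowing the visit.

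**Working it through.** No formula applies: the article gives no figure on this point to reproduce, and none from which a bias could be computed. The check is a comparison of statements.

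1. **What unblinded means here.** Sample size and recruitment says that there is no control group and that each patient is his or her own comparator. Every participant receives DBS, so there is no allocation to conceal. The only thing that can be masked in a comparison is the time point. Read literally, awareness of treatment among all investigators covers this, and no outcome is excepted.

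2. **Which outcomes could be masked.**
   - The four main scales, the quality-of-life scale, the Aberrant Behavior Checklist and the SIB logs are completed by people who live with the treatment. They cannot be masked in this design.
   - FDG-PET and electrophysiologic data do not depend on caregiver opinion, but neither measures behaviour.
   - Actigraphy measures movement with a device. It is the only listed behavioural outcome whose processing can be separated from knowledge of the visit.

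3. **Where knowledge of the visit could act.** The listed markers are maximum amplitude, minimum amplitude, variance, peak to peak and an entropy measure from the Fourier transform, five in all. Each is computed, so the formula leaves no room for opinion. Three steps around it do:
   - deciding which hours of a two-week recording count as worn;
   - deciding which bursts are artefact (maximum, minimum and peak to peak rest on extreme values, so they respond directly to which bursts are removed);
   - deciding which marker to report, since none leads.

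4. **Standing of the outcome.** Actigraphy is labelled additional, and wearing the device is optional in the follow-up schedule (Table 3). Feasibility and safety sets a projected completion of 50% for PET and actigraphy together: 0.50 × 6 = 3 children. The markers are of stereotypies, not of injury. The primary objectives are feasibility and safety, and the threshold for progression is recruitment.

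5. **Amount of work.** Clinical outcome measures gives one baseline period and follow-up at weeks 12, 26 and 52, which is at most 6 × 4 = 24 recordings. Table 3 omits week 26, and Follow-up counts three periods, which gives at most 6 × 3 = 18. The schedule needs reconciling, but on either count the coding is a small task.

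**The case against.** The strongest reply is that this asks a journal article for details that it commonly leaves to a full protocol or analysis plan. File coding, wear-time rules, artefact rules and choice of marker all belong there, and their absence is not an error. That stands for the rules themselves. What remains is that the article does speak on the subject: it declares all investigators aware and makes no exception, in a text that otherwise gives the device, wrist, wear duration, features and software. If files are already coded, one qualifying clause settles the matter.

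A second reply is that computed features are not subjective ratings. This also stands. A reader might infer that actigraphy carries the same observer bias as the caregiver scales and so cannot serve as an independent check. The documents do not support that, because only the discretionary steps around the computation are open to influence.

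A reader might also infer that unmasked investigators do process the files, or that a marker will be picked after the results are seen. The article says neither. It does not name the processor, and it presents the markers simply as a list.

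Third, the article never offers actigraphy as a check on the scales. It is optional, worn on one wrist and aimed at stereotypies. Masking cures none of those limits, nor selective wearing by families who know the treatment. This is correct, and it is why the point is minor.

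Counting the chance of a false positive across five markers would not size the problem. That chance is the same whether files are masked or not, and it depends on correlations that the article does not give.

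**Conclusion.** The point holds in a limited form. The blinding statement covers all investigators without exception, no masking of time point is described for actigraphy, and knowledge of the visit could influence wear-time, artefact and reporting choices. This weakens actigraphy as a supplement to the unblinded ratings but does not invalidate it.

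The conclusion rests on two assumptions. The first is that awareness of treatment in a single-arm trial amounts to awareness of time point. The second is that whoever processes the files falls under the statement about all investigators. The second is an inference.

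Neither the size nor the direction of any bias can be derived from the documents. This is a cheap improvement to an optional, exploratory outcome. It has no bearing on the primary feasibility and safety conclusions or on the recruitment threshold for progression.

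**What to change.** Qualify the blinding statement in Data management and statistical analysis along these lines: patients, caregivers and treating staff are unblinded. Actigraphy files, however, are given random codes by existing study staff, with dates and visit labels removed. Wear-time and artefact rules and one leading marker are fixed before decoding. All files are processed, and the results locked, under code before visits are revealed. Say also who processes the files. If this is already the practice, the qualifying sentence alone is enough.

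Clock time within a recording can be kept, since wear-time rules are likely to need it. Only calendar dates and labels have to go.

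The cost is a few hours of file coding and a short delay before actigraphy results can be viewed. No extra procedure or patient burden is involved, and the open-label design and clinical care are unchanged.

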## Discussion

The current paper presents a single-cohort, open-label, non-randomized, prospective pilot trial for the first controlled study of DBS of the NAcc for severe, refractory SIB in children and youth with ASD. This study is important to understand feasibility, safety, and treatment response. It is critical to establish feasibility of DBS for this novel indication and vulnerable patient population.

The rapid expansion of DBS indications in adult pathologies has allowed for treatment of many psychiatric diseases [58–60]. It is expected that the adaptation of DBS for children will be feasible for SIB. The early treatment of SIB in childhood could potentially be beneficial during critical windows of development such as in the adolescent or young adult years. The largest feasibility challenge of this study will be recruitment of vulnerable participants. This is mitigated by a multi-disciplinary team who are familiar with the patient population and the trial to allow for multiple sources of referral. Furthermore, results of a pilot trial should greatly improve recruitment in a future definitive trial. The use of multiple clinical measurement tools may help determine the optional composite measure of responsiveness of SIB to DBS. Although the quantitative data may not be rigorous enough to calculate a minimally clinical important difference, an estimated effect size may help determine sample size. Careful measurement and analysis of feasibility in this unique trial will be critical in the design of future research.

SIB has a high prevalence in several genetic disorders, such as Lesch-Nyhan disease and Fragile X syndrome, suggesting the pathophysiology of SIB may at least in part be rooted in neurobiological as well as neurodevelopmental etiologies [6]. Conversely, environmental triggers, such as novel sensory stimuli or changes in routine, often trigger the onset of episodes of SIB [61]. In patients with ASD, SIB frequency has a direct correlation with ASD severity [62]. The phenotype of SIB in patients with ASD shares similar features to phenotypic behaviors in other psychiatric conditions affecting children and adults, including OCD, attention-deficit hyperactivity disorder, and Tourette’s syndrome [63]. These conditions may be comorbid and share a common behavioral phenotype characterized by repetition, rigidity, invariance, and sometimes inappropriateness [38, 63]. Improved understanding of neural circuitry and effective DBS treatment options for one indication may enrich the understanding of the related diagnoses and their neurobiological pathophysiology.

DBS is a minimally invasive surgical option for patients with refractory SIB. It is reversible, adjustable and has a well-tolerated safety profile. Although increasingly offered to children for expanding indications, it is often considered an experimental therapy in this context. A proposed ethical framework to guide the conduct of DBS in children has been proposed, to which this study adheres [64]. The principles of this framework include viewing outcomes in a developmentally relevant context, cautiously applying adult data, and weighing the timing of the procedure [64].

Adult data and experience regarding DBS are not directly applicable to children. As one example, most children will have surgery under general anesthesia, which may preclude microelectrode recordings. Second, stimulation settings are often adopted from adult literature, yet long-term effects for children are not yet fully understood [23]. Third, indications and decisions regarding timing for intervention are complicated in children as treatment decisions are made within the context of childhood development and disease natural history. For example, the natural history of Tourette’s syndrome is often to remit as children develop and therefore the indications for DBS in children are as-of-yet unknown [65, 66]. Finally, complications including infection, lead migration or wire fractures are probably higher in children [21] and side effects of DBS on the developing brain require further study. Moreover, these hardware-related adverse events may manifest differently in children and youth with ASD and repetitive or compulsive SIB, relative to other pediatric cohorts.

## Strengths and limitations

This is a prospective, pilot trial of six patients and analyses of clinical outcomes will be limited by the small cohort. The results of this trial should inform larger clinical trials of multiple institutions. Furthermore, there is a lack of consensus regarding the ideal clinical assessment tool to measure the severity and frequency of SIB events. The use of the CYBOCS-ASD, ISAS and the RBS-R questionnaires incorporates several aspects of SIB such as repetitive movements, degree of harm, and impact on functional activities.

